### Outcomes

A detailed description of study outcomes and outcome measures is presented in Table 3. KT tools are intended to impact end-user experience, including increasing knowledge, influencing healthcare decision-making, and use of healthcare resources/services. Comprehension and retention of health information is a key component of the patient experience, a determinant of care instruction follow-through, and the cornerstone of health literacy; therefore, parental knowledge of childhood AGE (e.g., cause of AGE, signs of dehydration, management of dehydration) over time will be assessed. In addition to comprehension, educational materials may also influence health decision-making; therefore, parental decision regret over time will be assessed to examine this impact considering the decision to bring their child to the ED for care. Additionally, minimum clinically important differences (MCIDs) will be identified for both knowledge and decision regret outcome measures. Finally, healthcare utilization post-ED visit will be explored as a potential future outcome.

**Table 3 Tab3:** Study outcomes, outcome measures, and data analysis methods by domain

Study domain	Outcomes and outcome measures	Data analysis methods
Scientific domain	*Quantitative*: Parental knowledge will be evaluated using an 8-item knowledge questionnaire developed by the research team. This questionnaire was informed by the abridged Caregiver Gastroenteritis Knowledge Questionnaire (CGKQ) [55] and tailored to key content in the experimental intervention video. It has been piloted with the target population (*n* = 15) and revised for clarity. It takes approximately 2.5 min to complete.	Correct responses will be given a score of one and are summed for a final score (0–8).
	*Quantitative*: Decision regret will be measured by the Decision Regret Scale comprised of five, 5-point Likert items. Internal consistency and validity have been demonstrated and it is a useful tool for measuring regret after health care treatment decisions, is easy to administer, takes less than 1 min to complete, and results in very few missing responses [56].	Items are scored individually and converted to a 0–100 scale following instructions in the user manual [57]. Items are summed and averaged for a final score, with regret increasing with a higher score.
	*Quantitative*: MCIDs will be calculated for the parental knowledge questionnaire and the decision regret scale using two methods: (1) data-driven approach and (2) patient-perspective [58].	Using a data driven approach, the standard error of measurement will be used as a proxy for the MCID. Using a patient perspective, patients will make global ratings on their own change via Likert items in post-intervention questionnaires 1 and 2. Both approaches will be compared to quantified changes in outcome measures and absolute change for both will be calculated [58].
	*Quantitative*: Post-ED healthcare utilization will be assessed by three items developed by the research team.	Descriptive statistics will be calculated.
	*Quantitative*: The perceived benefit and value of the KT intervention for pediatric AGE will be evaluated using four items developed by the research team and by examining the number of participants that request a video link after questionnaire 1.	Descriptive statistics will be calculated.
	*Qualitative*: The perceived benefit and value of the KT intervention for pediatric AGE will be also evaluated via a qualitative interview with a convenience sample of volunteer parents from the experimental intervention group.	Thematic analysis of interview data will be conducted.
Process domain	*Quantitative*: Consent rate will be measured by (1) percentage of people approached who consent to participate and (2) timing (date, time of day) of refusals.	Descriptive statistics will be calculated.
	*Quantitative*: Recruitment rate will be measured by (1) percentage of people who consented to participate and complete pre-intervention questionnaire, post-intervention questionnaire 1, post intervention questionnaire 2, and qualitative interview; and (2) timing (date, time of day) of recruitment.	Descriptive statistics will be calculated.
	*Quantitative*: Data completion will be measured by (1) percentage of missing/blank survey items and (2) percentage of drop-outs at post-intervention questionnaire 2.	Descriptive statistics will be calculated.
	*Qualitative*: Satisfaction with electronic platform will be evaluated in the qualitative semi-structured interview with a convenience sample of volunteer parents from the experimental intervention group.	Thematic analysis of interview data will be conducted.
Management domain	*Quantitative*: Data quality will be measured by number, type, and duration of technical problems (i.e., error messages, problems with internet connectivity, and lost data) with an online platform throughout the study period.	Descriptive statistics will be calculated.
	*Qualitative*: Parents’ willingness to participate in future, similar research will be evaluated by a qualitative interview with a convenience sample of volunteer parents from the experimental intervention group.	Thematic analysis of interview data will be conducted.
Resource domain	*Quantitative*: Time to collect data will be measured by (1) average length of time to complete study questionnaires and (2) average length of time (days) to complete post-intervention questionnaire 2 post-discharge.	Descriptive statistics will be calculated.
	*Quantitative*: The feasibility of using iPads to collect data in the ED with parents/caregivers will be measured by tracking the number of broken, lost, or stolen iPads, iPad chargers (including cord and plug), iPad cases, and WiFi hubs.	Descriptive statistics will be calculated.

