To address the research-practice gap in pediatric AGE and provide parents with a reliable, research-based information resource, our research team developed a 3-min whiteboard animation video using patient-oriented research methods [25]. Whiteboard animation videos are short, hand-drawn, and narrated videos optimized for online streaming. Video content was drawn from knowledge synthesis results of treatment and management strategies for pediatric AGE [1]. The video storyline was developed from a qualitative study (*n* = 15) that gathered and synthesized stories from parents/caregivers of children with vomiting and diarrhea who visited an ED for healthcare [8]. Video prototypes were reviewed, and a final version approved by pediatric emergency clinicians, research nurses, and parents. The video depicts a family with a sick child trying to determine whether medical attention is required. The family recalls an information sheet given to them at a hospital when their child was ill with the same symptoms at an earlier time. The family assesses their child using the information sheet and determines to monitor and manage the child’s illness at home until symptoms resolve. The family describes worsening symptoms that would require them to take their child to the emergency department. Artists, including a script writer, animators, and voice actor, were contracted to work with the research team to ensure high-quality video production.

Rigorous evaluation of the effectiveness of the whiteboard animation video is a critical next step. Given some uncertainty regarding the most appropriate methods for evaluating the effectiveness of KT tools for parents [26], including best outcome measures and parameters for sample size calculations, we have chosen to first undertake a pilot trial [27–29]. We are also interested in exploring the feasibility of using an electronic platform to assist with recruitment, intervention delivery, and data collection. The study objectives are listed in Table 1 according to four key pilot trial domains [27].

**Table 1 Tab1:** Study objectives

Pilot trial domains	Study objectives
Scientific domain	• To estimate the potential effectiveness of a digital knowledge translation tool for parents/caregivers about pediatric AGE. Effectiveness outcomes include knowledge, decision regret, and post-ED healthcare utilization.

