	• To identify the perceived benefit and value of KT tools for this population, including important components that enhance knowledge about childhood AGE and decision-making regarding choice to take child with AGE to the ED.
Process domain	• To identify whether using an electronic, web-based platform for intervention delivery and data collection is feasible with this population.
Management domain	• To describe this population’s willingness to participate in future, similar research (i.e., full-scale trial).
Resource domain	• To estimate time required for participants to complete data collection forms.
	• To identify whether using iPads to collect data is feasible with this population.

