### Interventions

The interventions take place in the ED waiting room post-triage assessment and prior to consultation with a physician. Post-intervention, all participants will receive standard medical care from healthcare providers. The study hospital has an information sheet about AGE; however, education about AGE including whether the information sheet is given to parents/patients is at the discretion of the attending physician.

For this study, the experimental intervention is a 3-min, whiteboard animation video about a family’s experience with pediatric AGE (URL: https://www.youtube.com/watch?v=5N3gMtvkCqk&list=PLxWz0fEGuv6o5LrEpvdsmQFs5zB1dIFR8&t=17s&index=12). The sham control condition is a 3-min standard video developed by the Centres for Disease Control and Prevention about hand washing for infection control (URL: https://www.cdc.gov/cdctv/healthyliving/hygiene/fight-germs-wash-hands.html) [30]*.* Parents will view either the experimental or sham control intervention once on an iPad in the ED waiting room post-triage assessment. Disposable headphones will be provided with the iPads to maintain blinding. At the end of data collection in the ED (post-intervention questionnaire 1), parents can opt to receive a link to their assigned video via email to view as often as they wish from their own device(s). Parents from the experimental intervention group that are participating in the qualitative interview will view the whiteboard animation video again at the start of the interview.

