### Randomization

Blocked randomization with randomly chosen block sizes will be used to ensure equal distribution of participants to the experimental and sham intervention study arms [31]. The blocked randomization sequence will be computer generated. Following sequence generation, the randomization sequence will be entered into a confidential module on the electronic platform. Once the sequence is entered, the randomization module will only be accessible using a confidential password. The randomization sequence will be kept confidential. It will be inaccessible to data collectors/outcome assessors and to the study participants.

After completing the pre-intervention questionnaire, including demographic information and baseline outcome data, on the electronic data collection platform, individual parents/caregivers will automatically be randomized to one of the study conditions (i.e., experimental intervention or sham control) based on the randomization sequence. This process will be seamless to participants. After viewing the study condition materials, participants will be automatically directed to post-intervention questionnaire 1. At study completion, all participants will receive a thank you email with links to both videos shown in the study.

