
### Data analysis

All data will be aggregated and analyzed. Quantitative data will be downloaded from a secure Canadian server to SPSS for data cleaning and analysis [42]. Data cleaning measures may include recoding into categorical variables and comparing and recoding free-text responses where appropriate. Descriptive statistics and estimation are the recommended focus of pilot/feasibility trials [43, 44]. Descriptive statistics (e.g., frequencies and measures of variation and spread) will be calculated to describe the study groups. Analyses by outcome measure are presented in Table 3. Analyses will be conducted based on intention-to-treat.

Initial data will be collected to perform a sample size calculation for a full-scale trial [43]. Estimation for knowledge and decision regret outcomes will focus on calculating confidence intervals of different widths to illustrate strength of preliminary evidence [43, 44]. Confidence intervals for the difference of means (paired) will be presented for both potential effectiveness outcome measures to account for repeated measures [45]. The confidence interval for the difference of means from time 1 to time 2 for both groups will be calculated to examine initial change scores and the difference of means from time 2 to time 3 for both groups will be calculated to examine sustained change score. Confidence interval widths for both initial and sustained change measures will be set at 99, 95, 90, 85, 80, and 75% and presented together alongside a minimum clinically important difference (MCID) in a graph [46]. If each confidence interval crosses both 0 and the MCID, this is inconclusive evidence of effect; however, if each confidence interval both excludes 0 and crosses the MCID, there is evidence of a potentially clinically important difference. A confidence interval that is above or equal to the MCID indicates that at this level there is a clinically meaningful difference between the groups.

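### Decision regret concerns a decision already made at randomisation, so neither planned change score shows an effect on decision-making or a sustained video effect

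*Protocol article*

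**What the plan says.** The Outcomes section reasons that "educational materials may also influence health decision-making" and, on that ground, that "parental decision regret over time will be assessed to examine this impact considering the decision to bring their child to the ED for care". Table 3 describes the Decision Regret Scale: "it is a useful tool for measuring regret after health care treatment decisions". Scores run from 0 to 100, and higher means more regret.

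Parents are approached in the ED waiting room (Recruitment). The Randomization section allocates them at this point: "After completing the pre-intervention questionnaire, including demographic information and baseline outcome data, on the electronic data collection platform". On timing relative to care, the Interventions section says: "The interventions take place in the ED waiting room post-triage assessment and prior to consultation with a physician". Standard medical care follows.

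The Data collection section gives the scale three times: at baseline (time 1), straight after the video (time 2), and through a link emailed on day 4 after discharge (time 3).

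The Data analysis section treats regret and knowledge alike: "The confidence interval for the difference of means from time 1 to time 2 for both groups will be calculated to examine initial change scores". A second paired interval, from time 2 to time 3, is meant to show sustained change. Both are read against 0 and the minimum clinically important difference (MCID). No time 1 to time 3 contrast and no baseline-adjusted between-arm contrast is named.

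**The concern.** The initial-then-sustained template suits knowledge, which a short video can raise at once. It suits regret less well. The parent is asked twice, minutes apart, about a decision that is already closed and whose consequences are not yet known. Time 3 comes after the consultation, the treatment and, for most children, the illness.

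The direction of a change is also open. The family in the video settles on handling the "illness at home until symptoms resolve". A parent who takes in that message may regret coming more, although the video has done its work. Another may feel reassured and regret coming less.

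The Background gives uncertainty about the best outcome measures and the parameters for a sample size calculation as reasons for running a pilot. If changes in regret are taken as evidence on decision-making, or the second change as persistence of a video effect, that misreading passes into the choice of outcome for the full-scale trial.

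**Working it through.** **1. When the decision was made.** The scale refers to bringing the child to the ED. Recruitment, baseline and allocation all take place in the ED, so the decision precedes randomisation for every participant, by design. This is as true at time 3 as at time 2.

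**2. Gap between the first two regret scores.** The protocol states no interval, so this is a nominal sum of its stated durations.

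- Video: 3 min in both arms (Interventions).
- Knowledge questionnaire: about 2.5 min (Table 3).
- Decision Regret Scale: under 1 min (Table 3).
- Listed order (Data collection): demographics, knowledge and regret at baseline; then the video; then knowledge and regret.

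End of first scale to start of second: 3 + 2.5 = 5.5 min.

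Start to start: at most 1 + 3 + 2.5 = 6.5 min, or 0.5 + 3 + 2.5 = 6.0 min if the scale takes half a minute.

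The forms themselves are in additional files not shown, so other orders are possible:

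- Shortest (regret last at baseline, first afterwards): 3 min end to start.
- Longest (regret before knowledge at baseline, last afterwards): 1 + 2.5 + 3 + 2.5 = 9 min start to start.

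The range is 3 to 9 min. Demographics have no stated duration and are left out. Interruptions in the waiting room could lengthen any of these figures.

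**3. What lies between the measurements.**

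| Contrast | What happens in between |
|---|---|
| Time 1 to 2 | Video and repeated forms; no physician consultation in the planned sequence |
| Time 2 to 3 | Consultation, standard care, discharge, at least 4 days, usually recovery (82% of cases resolve in 3 days or less, Data collection) |

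**4. What each contrast estimates.** Let e2 and e3 be the video-versus-sham effects on the regret score at times 2 and 3. Let c be the change from time 2 to time 3 that would occur under the sham video, through the visit, recovery and passage of time.

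- Within the experimental arm, time 2 to 3: (e3 − e2) + c. The video's part cannot be separated from c.
- Within the sham arm: c alone.
- Between arms, time 2 to 3: e3 − e2. If the effect were fully sustained (e3 = e2), this would be 0, so even this difference does not measure a sustained effect.
- Between arms at time 3, adjusted for time 1: e3, the effect present after the visit.

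**5. Direction.** The reading rule in Data analysis treats an interval at or above the MCID as meaningful, for both outcomes. On this scale upward means more regret. Nothing in the section says whether a rise or a fall counts in the video's favour.

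**The case against.** Regret always concerns a past decision, so a closed decision is no defect in itself. The video does come between times 1 and 2, and its content bears on whether a visit was needed. A between-arm difference in the time 1 to 2 change could therefore validly show that the video altered the parent's appraisal of coming. This stands. A reader might infer that the early measurement is uninformative, or that a near-zero change only means nothing happened; the documents do not support that.

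A reader might also hold that the scale may not be used until the outcome of the visit is known. Table 3 says only that it measures regret after treatment decisions, and the user manual is not to hand, so that cannot be claimed.

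Nor can it be said that the pilot has no quantitative measure of decisions the video could influence. Questionnaire 2 has three items on healthcare use after the visit, which depends on decisions still open at randomisation. The Table 1 phrase "decision-making regarding choice to take child with AGE to the ED" belongs to an objective on the perceived value of such tools, which has its own items and interviews.

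Two limits of wording also stand. Triage has been done, so the early scores precede consultation and standard care, not all care. And the protocol calls intervals that cross both 0 and the MCID inconclusive; it does not call them evidence of no effect.

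Finally, a pilot may reasonably try a scale at several times to see when it responds. That supports keeping the time 2 score, but not treating its change as evidence on decision-making.

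**Conclusion.** The point holds in a limited form. Both planned regret contrasts are affected. The first lies wholly before the consultation, over a nominal 6 minutes or so, and can show at most a changed appraisal of the decision to come. The second mixes any video effect with the visit and recovery. Neither supports the link to decision-making drawn in the Outcomes section, and the 0/MCID rule gives no direction for this scale.

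Time 3 does not reopen the decision either. A time 3 comparison is sounder because it compares randomised arms after the visit, when the parent can judge what came of it. It remains an effect on regret about that visit.

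This rests on the forms being completed before the physician arrives, which the sequence implies but does not guarantee, and on the paired intervals being calculated within each arm, as Data analysis reads. The size of any resulting bias cannot be computed, since no regret means, standard deviations or MCID are given. The change is worth making because it improves what the pilot hands on; it does not call the rest of the pilot into question.

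**What to change.** In Data analysis, treat regret separately from knowledge:

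- **Main estimate:** the experimental-versus-sham difference in regret at time 3, adjusted for the time 1 score, with the planned set of confidence levels, described as an effect on regret about the ED visit.
- **Secondary:** the between-arm difference in the time 1 to 2 change, reported as immediate appraisal and responsiveness of the scale, not as evidence on decision-making.
- **Time 2 to 3:** if still shown, present it descriptively and do not call it a sustained video effect.
- **Direction:** state that neither a rise nor a fall is labelled benefit or harm unless a direction is justified before the data are seen. Align the sentence in Outcomes that ties regret to decision-making.

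This needs only wording and one regression on data already planned. There are two costs. Time 3 depends on emailed follow-up and so on drop-out, which should be reported by arm beside the estimate. And the immediate regret contrast is no longer a headline effectiveness result. Items on what the parent would do at a future episode could be added, but the correction does not need them.

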Knowledge translation (KT) is defined as the synthesis, exchange, and application of knowledge to improve the health of individuals, provide more effective health services and products, and strengthen health care systems [12]. Current approaches to KT research are largely focused on aligning the behaviors of health professionals with best research evidence; however, there are increasing calls for KT interventions for health consumers to influence health knowledge, decision-making, and service utilization [13], especially given the many alternative health options open to parents through the Internet. At present, there is little guidance on the most effective approach, content, duration, and intensity of education for this diverse population [14–16]; however, it is hypothesized that providing evidence-based child health information to parents and families has the power to ensure consistent parental management of child health over time and across settings [17], increase effective health decision-making [18], and reduce health system costs [18]. It is critical to generate empiric evidence to help determine the optimal modes for delivering evidence-based information to parents and families.

At present, it is routine practice to provide health education to parents seeking care for their children in EDs to guide care after discharge [17]. Typically, education is provided at the end of the emergency department visit when parents are tired and anxious to leave, making them less likely to ask important questions and retain information [19]. Additionally, information provided verbally is often brief [20] and written information is often too complex for most adults to comprehend [21, 22].

Since online tools (e.g., podcasts, e-books, animations, and infographics) are low or no cost, easily accessible, and can be consumed on demand, they hold promise as an effective approach to KT for parents and caregivers seeking research-based information related to child health [23, 24]. Additionally, online platforms allow content to be viewed as frequently as needed, which may improve information retention and compliance [24].

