The following data will be collected over the course of this study:Pre-intervention questionnaire (baseline, see Additional file 1): Participants will complete a pre-intervention questionnaire that includes demographics, knowledge questionnaire, and Decision Regret Scale within the iCare Adventure platform on the iPad.**Participants will then be randomized to view the study intervention or the standard care intervention within the iCare Adventure platform on the iPad. This process will be seamless for the participants.Post-intervention questionnaire 1 (immediate, see Additional file 2): After viewing the intervention, participants will complete the knowledge questionnaire and Decision Regret Scale a second time. In addition, participants will complete two items assessing their own performance on the knowledge questionnaire and Decision Regret Scale and one item regarding the perceived value and benefit of the KT tool. They will also be asked if they would like a video link emailed to them. At the end of this questionnaire, parents will be informed that the post-intervention questionnaire 2 will be emailed to them 4 days after this ED visit for completion at their earliest convenience. Experimental intervention group parents will be asked about participation in a qualitative focus group at this time.Post-intervention questionnaire 2 (4–14 days post-ED, see Additional file 3): Participants will be emailed a secure link on day 4 post-ED discharge to complete the knowledge questionnaire and Decision Regret Scale a third time, two items assessing their own performance on the knowledge questionnaire and Decision Regret Scale, three items related to healthcare utilization, and three items related to the perceived value and benefit of the KT tool (if applicable). Reminders to complete post-intervention questionnaire 2 will be sent to those who have not completed the survey every third day (day 7, 10, 13) to complete the survey by day 14 post ED-discharge. Previous research has demonstrated that 82% of AGE cases are resolved in 3 days or less and 14 days [40] represents the outer limit for pediatric AGE resolution [41].Post-intervention semi-structured interview (sub-sample of experimental group, see Additional file 4): Participants in the experimental group indicating willingness to participate in an in-depth, semi-structured, qualitative interview will be contacted via telephone after completion of post-intervention questionnaire 2. Up to three phone calls will be made to establish interview date/time. Qualitative interviews will focus on satisfaction with iCare Adventure platform, perceived benefit and value of the KT intervention, and willingness to participate in future, similar research.

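### The stated knowledge contrasts show immediate comprehension (time 1 to 2) and decay or catch-up (time 2 to 3); none estimates what the video adds to usual AGE education

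*Protocol article*

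**What the plan says.** Table 1 of the Protocol article lists knowledge among the effectiveness outcomes. Table 3 (Outcomes) describes an eight-item questionnaire scored 0 to 8. It was developed by the team, informed by an existing caregiver questionnaire, and "tailored to key content in the experimental intervention video".

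Knowledge is measured three times: at baseline (time 1), in questionnaire 1 (time 2), and in questionnaire 2, emailed on day 4 after discharge (time 3). On time 2, the Randomization section says: "After viewing the study condition materials, participants will be automatically directed to post-intervention questionnaire 1". The Data collection section agrees: "After viewing the intervention, participants will complete the knowledge questionnaire and Decision Regret Scale a second time".

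Under Interventions, both videos are shown in the waiting room before the physician is seen, and the sham video is about hand washing. Then: "Post-intervention, all participants will receive standard medical care from healthcare providers". The hospital has an AGE information sheet, but "education about AGE including whether the information sheet is given to parents/patients is at the discretion of the attending physician".

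The Data analysis section fixes two contrasts, each a paired change calculated for both groups: time 1 to time 2 (initial change) and time 2 to time 3 (sustained change). Both get intervals at six levels from 99% to 75%, drawn beside an MCID. One reading rule covers both. Intervals that exclude 0 and cross the MCID point to a difference that may matter clinically. An interval at or above the MCID is taken to show that the groups differ to a clinically meaningful degree.

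**The concern.** At time 2 the video arm has just heard the material on which it is tested. For the sham arm, no AGE-specific teaching has yet been described. Some difference at that point is close to built in. It tells us that parents understood the video, not that the video improves on what parents would otherwise learn in the ED.

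The second question is the one the protocol motivates. The Background says "At present, it is routine practice to provide health education to parents seeking care for their children in EDs to guide care after discharge", and goes on to argue that such education is often brief, badly timed or too complex. Whether the video improves on it can be judged only after usual education has had its chance, which is at time 3. The plan collects time 3 in both arms but uses it only as a change from time 2. A reader following the plan would apply the clinical-importance rule to a comprehension check and to a decay measure, and would have no interval for the added value of the video when planning the full-scale trial.

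**Working it through.** There is no stated effect, SD or sample size to reproduce. The check is first one of sequence, then of what each contrast can estimate.

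**Sequence (Interventions, Randomization, Data collection)**

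1. Time 1 test, then randomization.
2. Video: AGE content, or hand washing.
3. Time 2 test, directly after viewing.
4. Physician consultation; AGE teaching and information sheet at the physician's discretion, both arms.
5. Discharge; time 3 test emailed on day 4.

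Time 2 precedes usual education and time 3 follows it.

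**What each contrast estimates**

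Let the mean change from time 1 to time 2 be g (video) and s (sham), and from time 2 to time 3 be h (video) and u (sham). Baseline means are equal in expectation by randomization.

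| Contrast | Video | Sham | Video minus sham | Meaning |
|---|---|---|---|---|
| Time 1 to 2 (stated) | g | s | g − s | immediate comprehension |
| Time 2 to 3 (stated) | h | u | h − u | decay or catch-up |
| Between arms at time 3 (not stated) | g + h | s + u | (g + h) − (s + u) | added value after usual education |

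The third row equals the sum of the first two, so its point estimate could be pieced together among parents who answered all three tests. Its interval could not: the two changes share the time 2 score and are correlated. The stated intervals are also within-group, although the reading rule speaks of a difference between groups.

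**Numerical illustration (all values assumed)**

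Take g = 2.0, s = 0, h = −0.5 (net of anything the video arm learns from usual education), and u = 0.5 to 1.0, on the 0 to 8 scale.

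- Time 1 to 2: 2.0 − 0 = 2.0 in favour of video.
- Time 2 to 3: −0.5 − 0.5 = −1.0, or −0.5 − 1.0 = −1.5, in favour of sham.
- Time 3 between arms: (2.0 − 0.5) − 0.5 = 1.0, or (2.0 − 0.5) − 1.0 = 0.5, in favour of video.

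The first stated contrast is two to four times the time 3 difference, and the second has the opposite sign.

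**What it would mean for planning (assumed effects; illustration only)**

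Two-sided alpha 0.05, power 80%, equal arms, normal approximation: n per arm = 2(1.960 + 0.842)² / d² = 15.70 / d², and power = Φ(d√(n/2) − 1.960).

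For an immediate effect of 0.8 SD, n = 15.70 / 0.64 = 24.5, so 25 per arm.

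| Share of effect left at time 3 | d | n needed per arm | Power with 25 per arm |
|---|---|---|---|
| 75% | 0.6 | 44 | about 56% |
| 50% | 0.4 | 99 | about 29% |
| 25% | 0.2 | 393 | about 11% |

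Starting from 0.5 SD (63 per arm), the needs are 112, 252 and 1005 per arm.

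**The case against.** The best defence is that the wording is cautious and the structure sensible. Table 1 speaks of potential effectiveness, Data analysis presents the intervals as preliminary evidence, and initial change is kept apart from sustained change. Writing a knowledge test to match what an intervention teaches is ordinary practice, and the domains named under Outcomes (cause, signs and management of dehydration) are general AGE knowledge. An immediate test is legitimate in a pilot. All of this stands, but none of it supplies the missing contrast or explains why one rule serves both changes.

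The size is also open. Parents may ask for the video link and watch again, which could limit forgetting. The Background's own view of usual education suggests that sham parents may catch up little. The eight items are not shown, so some overlap with hand-washing content cannot be excluded, and teaching at triage is not described either way.

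Three stronger inferences are tempting and are not supported:

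- That the plan declares the video effective from time 2. It does not; it reads the result as preliminary evidence of a difference that may be clinically important.
- That the time 2 difference will size the full-scale trial. Data analysis says only that pilot data will feed that calculation, and names no outcome or time point.
- That questionnaire 2 fails to record whether usual AGE education was received. The questionnaire is an additional file that is not shown. Comparing arms within answers to such an item would also condition on something that happens after randomization, so it would not be a randomized comparison.

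**Conclusion.** The point holds as a matter of contrast and interpretation. The time 1 to time 2 change reflects immediate comprehension of video-matched items, against no AGE-specific teaching described. The time 2 to time 3 change reflects decay or catch-up and can favour sham even when the video arm remains ahead. Neither estimates what the video adds to usual education, although the data to do so will be collected. This is not detail that an article would leave to a fuller document: Data analysis itself fixes both contrasts and the rule for reading them.

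The sequence and the algebra rest on the text. The size does not: every effect used above is assumed, and the loss of power would arise only if time 2 were chosen to size the next trial, which the document leaves open. The correction is worth making now because it is cheap and bears on what the pilot is for.

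**What to change.** In Data analysis:

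1. Label the time 2 knowledge result as immediate comprehension, and do not read it against the MCID as evidence of potential effectiveness.
2. Add a between-arm difference in knowledge at time 3, adjusted for the time 1 score (analysis of covariance), with the same six confidence levels. Name it as the estimate of potential effectiveness that is read against the MCID and considered when planning the full-scale trial.
3. Keep the time 2 to time 3 changes as a description of retention in the video arm and catch-up in the sham arm.

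The cost is a few sentences and one additional model. No new item, visit or change to recruitment, randomization or care is needed. The drawback is that the knowledge effect carried forward will probably be smaller, and it rests on those who answer questionnaire 2, so response by arm should be shown beside it.
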